**Methods/Design:**

Patients with sHPT (intact parathyroid hormone > 10 times above the upper limit of normal) on long term dialysis (>12 months) will be randomized either to TPTX or TPTX+AT and followed for 36 months. Outcome parameters are recurrence rates of sHPT, frequencies of reoperations due to refractory hypoparathyroidism or recurrent/persistent hyperparathyroidism, postoperative morbidity and mortality and quality of life. 50 patients per group will be randomized in order to obtain relevant frequencies of outcome parameters that will form the basis for a large scale confirmatory multicentred randomized controlled trial.

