**Discussion:**

sHPT is a disease with a high incidence in patients with chronic renal failure. Even a small difference in outcomes will be of clinical relevance. To assess sufficient data about the rate of recurrent sHPT after both methods, a multicentred, randomized controlled trial (MRCT) under standardized conditions is mandatory.

Due to the existing uncertainties the calculated number of patients necessary in each treatment arm (n > 4000) makes it impossible to perform this study as a confirmatory trial. Therefore estimates of different outcomes are performed using a pilot MRCT comparing 50 versus 50 randomized patients in order to establish a hypothesis that can be tested thereafter.

If TPTX proves to have a lower rate of recurrent sHPT, no relevant disadvantages and no higher morbidity than TPTX+AT, current surgical practice may be changed.

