### Current treatment options

Three different surgical procedures are reported in the literature following the first PTX for secondary HPT in 1960 [26]: subtotal PTX (removal of three and a half glands and leaving half of a gland as a remnant in the neck [27,28], total PTX with autotransplantation (TPTX+AT) of some of the excised tissue into defined areas (forearm muscle, anterior tibial muscle or subcutaneously [28-31], and total parathyroidectomy without autotransplantation (TPTX) [32,33]. Ogg [34] initially reported that TPTX provides a feasible therapeutic option in patients who are on chronic dialysis therapy. However, TPTX was not introduced into clinical practice because of the potential complication of adynamic bone disease or severe ongoing hypocalcemia. Therefore subtotal PTX or TPTX+AT, both supplemented with thymectomy, are currently considered as the standard procedures in the treatment of sHPT [28,32,35,36].

However, both procedures leave a fragment of activated, proliferated parathyroid tissue, though at different sites. Since the pathophysiological condition of chronic renal failure and maintenance dialysis continues, the growth stimulus persists and may cause recurrent sHPT at the site of the remnant. Although relapse of HPT has been observed at different intervals after initial surgery, it is quite clear that the incidence of recurrent disease increases with time [37,38]. A wide range of recurrence rates has been published for both procedures (range 5–80%). This variation is dependent on the definition of recurrent sHPT and variability in follow up periods given in different series for both techniques [32]. Recurrence-rates after TPTX+AT or subtotal PTX after a median follow up of 36 months are reported to be between 10% and 12% [31,39-41]. All other clinically relevant outcome parameters (mortality and morbidity) do not differ significantly between TPTX+AT and subtotal PTX [28,40,42].

The site of recurrence in patients after TPTX+AT is located in approximately 80% at the graft (Figure 1) and in 20% in the neck [24,36,43-47].

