**Figure 1 F1:**
[figure not shown]
This figure shows the enlargement of a parathyroid autograft in a patient with recurrent secondary hyperparathyroidism, demonstrated by a knob underneath the scar.

Graft-dependent recurrent sHPT after TPTX+AT can easily be cured by excision of the parathyroid autotransplant under local anaesthesia. If an operation is necessary for recurrent sHPT after subtotal PTX, reexploration of the neck is mandatory in all patients including the necessity of general anaesthesia and the increased risk of recurrent laryngeal nerve palsy [48]. Therefore, in case of recurrent disease, subtotal PTX as preceding procedure is clearly inferior to TPTX+AT given equal effectiveness for the initial treatment of sHPT.

Total parathyroidectomy without autotransplantation and without routinely performed thymectomy (TPTX) may provide an alternative strategy to the currently performed procedures mainly because of the reported lower rate of recurrent sHPT of 0–4% during long-term follow up [32,36]. Patients after TPTX did not develop hypoparathyroidism [32,36] and particularly adynamic bone disease as initially expected [32,36,49-52]. Moreover, patients lacking a parathyroid remnant maintained on a noncritical calcium/phosphate product during the ongoing follow-up, compared to individuals with persisting parathyroid secretion after PTX [38].

One explanation for the absence of serious adverse events may be that thymectomy was not performed on a regular basis. The inferior parathyroid glands and the thymus derive together from the third pharyngeal pouch. Even in case of resection of all four parathyroid glands (TPTX) residual microscopic parathyroid tissue or supernumerary glands may be located in the thymus preventing the patients to develop hypoparathyroidism and its sequelae [29,40,53-56].

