## Methods/Design

### Objectives of the study

The objective of this study is to compare different outcomes of TPTX and TPTX+AT for sHPT over a three-year follow-up period. The information gained will be used for further clinical trials.

The primary objective of this trial is to assess a better estimate of the rates of recurrence of both methods. This shall establish a hypothesis that can be tested thereafter.

Secondary objectives are divided into those occurring intraoperative, postoperative until discharge and after discharge until 36 months postoperatively.

Intraoperative categories comprise the duration of the surgical procedures, the expertise of the responsible surgeon, and complications and findings during surgery.

Within the postoperative setting until discharge, the frequency of persistent hyperparathyroidism, the morbidity and the length of hospital stay are noted. During follow up, the frequency of persistent or recurrent sHPT, the frequency of subsequent parathyroid autotransplantation due to refractory hypoparathyroidism, the frequency of reexploration of the neck or the parathyroid autograft, the frequency of irreversible paralysis of the recurrent laryngeal nerve, the change of symptoms related to sHPT as well as the change in quality of life and finally the incidence of death are recorded.

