#### Descriptive analysis

Baseline characteristics as well as efficacy and safety endpoints will be analyzed with descriptive methods. The description of continuous variables includes at least: number of observations, mean, standard deviation, median, minimum and maximum in the trial population. The description of nominal variables includes at least the number and percentage of patients belonging to the relevant categories in the trial population as well as in each treatment group. In order to improve the presentation of the observed data, graphical methods will be applied.

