## Discussion

TOPAR PILOT is a randomized controlled multicentred pilot trial to generate high quality evidence comparing the outcomes of TPTX+AT vs. TPTX. Since secondary hyperparathyroidism is a very common disease in patients with chronic kidney failure, even a small difference in outcomes will be of clinical relevance. If TPTX proves to have no relevant disadvantages and a smaller rate of recurrent sHPT, a large scale confirmatory study will be launched to establish this approach.

Recent reports comparing TPTX+AT to TPTX were retrospective, underpowered or not designed as RCT's. No unique definition for recurrent sHPT was used to calculate the rate of recurrent sHPT. The follow up periods of former studies have often been too short and were not standardized (table 2). Therefore we will perform a follow up of each patient at 6, 12, 24 and 36 months after surgery to allow an assessment of the medium/long term effect of the different surgical treatments.

**Table 2 T2:** Rate of recurrent sHPT after TPTX or TPTX+AT

**Reference**	**TPTX+ AT n**	**TPTX n**	**Routinely performed thymectomy**	**Mean length of follow – up (months)**	**Recurrent sHPT^1 ^(%)**
Rothmund et al. 1991 [29]	20		yes	43	0
Zaraca et al. 1999 [58]	18		no, only if palpation was suspicious or parathyroid gland was missing	28	10
Walgenbach et al. 1997 [46]	67		yes	18	4.5
Walgenbach et al. 1998 [59]	86		yes	24	3.5
Henry et al.1990 [40]	152		no	30	10.5
Welk and Alix 1987 [60]	21		n.m.	33	24
Hampl et al. 1991 [37]	13		yes	33.5	76.5
Chou et al. 2002 [61]	75		n.m.	54	13.3
Bessell et al. 1993 84	42		n.m.	40	9.5
Dotzenrath et al. 2003 [62]	99		yes	51	6
Korzets et al. 1987 [63]	19		n.m.	6–60	26.3
Kinnaert et al. 2000 [31]	59		no	38	12
Tominaga et al. 1997 [39]	519		yes	36	10
				60	20
Ockert et al. 2002 [32]	11		no	38	45
		11	no	22.5	0
Kaye et al. 1993 [64]		13	n.m.	46	0
Higgins et al. 1991 [44]	34		no	72	80
		9	no	10	0
Nicholson 1996 [36]	13		no	24	16
		24	no	24	0
Saunders et al. 2005 [52]		55	no	29	4
Stracke et al. 1999 [35]		20	n.m.	20	4
Hampl et al. 1999 [65]		11	no	26	0
Ljutic D et al. 1994 [66]		43	no	104	2.3

n.m. = not mentioned

^1 ^Recurrent sHPT is defined as an increase of PTH > 5 fold above normal value after more than 6 months after initial PTX and after initial (postoperative) normalization of PTH.

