### Surgeon's expertise bias

In this study, stratification for surgeon's skill is made and measured data will be analyzed by analysis of variance in regard to surgeon's skill and centre. Due to this analysis of variance, bias of centre effects and surgeon's skill should be reduced.

The trial will only be performed in high volume centres (defined as more than 15 parathyroidectomies per year for sHPT) minimizing bias due to learning effects. No additional surgical training has to be done as the neck exploration is the same in TPTX as in the standard procedure of TPTX+AT.

In conclusion, this is the first randomized controlled multicentred trial comparing different surgical techniques in parathyroid surgery for sHPT. If significant, the results will be revised by a large scale confirmatory study. The results may change the current surgical practice thereafter.

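### The confirmatory trial is made conditional on the pilot being significant or proving a lower recurrence rate, although the pilot is an estimation study in which 50 per arm usually cannot show this

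*Protocol article*

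**What the plan says.** The design sections describe an estimation pilot. Under Objectives of the study: "The primary objective of this trial is to assess a better estimate of the rates of recurrence of both methods". The abstract's Methods/Design gives the purpose of the sample size as: "50 patients per group will be randomized in order to obtain relevant frequencies of outcome parameters". Under Descriptive analysis: "Baseline characteristics as well as efficacy and safety endpoints will be analyzed with descriptive methods". The sections on bias and blinding and the Discussion both call the study non-confirmatory, and use that as the reason for having no sham procedure.

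Three statements about what follows the pilot are comparative:

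- Closing paragraph, under Surgeon's expertise bias: "If significant, the results will be revised by a large scale confirmatory study". The next sentence places any change of practice after that study.
- Discussion, opening paragraph: "If TPTX proves to have no relevant disadvantages and a smaller rate of recurrent sHPT, a large scale confirmatory study will be launched".
- Abstract, Discussion: if TPTX proves to have a lower recurrence rate, "no relevant disadvantages and no higher morbidity than TPTX+AT, current surgical practice may be changed". No confirmatory trial is mentioned in that sentence.

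**The concern.** A study built to estimate two rates is given a next step that depends on a comparison it was not sized to make. The three statements also differ. One asks for significance, one for proof of a smaller rate, and the abstract goes straight from the pilot's result to a possible change of practice.

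Two things are at stake. If the significance condition were followed, a real difference of the size the article cites would usually be missed and the confirmatory trial not launched. That trial would also almost never be launched if the two procedures have equal recurrence, which is the premise of the article's own non-inferiority calculation. And a reader of the abstract alone could take a pilot of 100 patients as a sufficient basis for judging morbidity.

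**Working it through.** **Inputs**

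- 50 per arm (abstract; Number of patients needed).
- TPTX+AT recurrence 10–12% at a median of 36 months (Current treatment options).
- TPTX: "the reported lower rate of recurrent sHPT of 0–4% during long-term follow up" (same section).
- Equal risks of recurrence, taken as 10% (Number of patients needed).
- Assumption: two-sided 5% test. The article names no test or level for comparing recurrence in the pilot, so Fisher's exact test and the uncorrected chi-square are both shown.

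**Step 1. The article's own figure.** The margin is printed as 1588. Read as an odds ratio it is (0.15/0.85)/(0.10/0.90) = 1.588. On the log odds ratio scale with both risks at 10%, one-sided 5% and 80% power:

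n = 2(1.645 + 0.842)² / (0.10 × 0.90 × (ln 1.588)²) ≈ 643 per arm.

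This is within 2% of the stated 656. Simulation at 656 per arm gives 80.3% power. The same calculation at 50 per arm gives about 17% power, so the pilot is also far too small for the non-inferiority question.

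**Step 2. How often is the pilot significant in favour of TPTX?** Sum P(x)·P(y) over all pairs of recurrence counts (x of 50, y of 50) with p ≤ 0.05 and TPTX lower:

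| True rates, TPTX+AT vs TPTX | Fisher | Uncorrected chi-square |
|---|---|---|
| 10% vs 4% | 9% | 20% |
| 12% vs 4% | 17% | 30% |
| 10% vs 2% | 19% | 38% |
| 12% vs 2% | 31% | 51% |
| 10% vs 0% | 38% | 75% |
| 12% vs 0% | 56% | 87% |

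With both rates at 10%, a significant result in either direction occurs in 1.8% (Fisher) to 5.1% (chi-square) of pilots.

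By the normal approximation, 80% power would need 283 per arm for 10% vs 4% and 180 per arm for 12% vs 4%.

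**Step 3. What does a significant pilot look like?** With no recurrence after TPTX, Fisher's test gives p = 0.056 for 5 vs 0 and p = 0.027 for 6 vs 0. Significance then needs an observed gap of at least 6/50 = 12 points. The cited rates imply true gaps of 6 to 12 points (10 − 4 to 12 − 0), so a significant pilot would tend to overstate the effect.

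**Step 4. If proving a smaller rate means only an observed lower rate.** The same enumeration gives the probability that TPTX has fewer recurrences:

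- both 10%: 43%
- TPTX worse, 12.5% vs 10%: 29%
- 10% vs 4%: 84%
- 10% vs 2%: 94%

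**Step 5. What the pilot can deliver.** The exact 95% interval for 5/50 is 3.3–21.8%, and for 2/50 it is 0.5–13.7%. The half-width for the risk difference at 10% vs 4% is 1.96 × √(0.10 × 0.90/50 + 0.04 × 0.96/50) = 0.099, about 10 points. For morbidity, 0/50 events has an exact upper limit of 1 − 0.025^(1/50) = 7.1%.

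**The case against.** **These are discussion remarks, not a formal rule.** No Methods section sets a test, level or criterion for proceeding, and the Methods text already describes estimation. That is fair, and it limits the severity. But these sentences are the only ones in the article that say when the confirmatory study follows, and they conflict with the Methods.

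**A reader might infer that the pilot is meant to change practice by itself.** The article as a whole does not support that. The closing paragraph places practice change after the confirmatory study, the Discussion speaks only of launching that study, and the abstract says practice may change, after stating that the hypothesis is to be tested later. The abstract sentence omits the middle step, and that is all that can be held against it.

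**A reader might infer that 50 per arm can never show a difference.** That is too strong. The cited TPTX range includes 0%, and five of the eight TPTX rows in Table 2 show 0%. At 0%, chi-square power is 75–87%. However, the three non-zero rows hold 55 + 20 + 43 = 118 of the 186 TPTX patients. Weighting by patients gives (55 × 4% + 20 × 4% + 43 × 2.3%)/186 ≈ 2%, although follow-up differs between series. A significant result would also keep its false-positive control; its weakness is imprecision and overstatement.

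**A lower observed rate does carry information.** 84% against 43% is not nothing, a false pass leads only to another trial, and the Discussion also requires no relevant disadvantages. All of this stands, so the evidence is weak rather than absent.

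**A reader might infer that the 15% drop-out allowance should have enlarged the pilot.** It belongs to a powered confirmatory sample. The pilot claims no power, so there is no required number to inflate.

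**Conclusion.** The concern holds as a contradiction between the stated purpose and the stated next step. Over true TPTX rates of 2–4%, a significance condition would be met in 9–31% (Fisher) or 20–51% (chi-square) of pilots, and under equal 10% risks in about 2–5%. A non-significant pilot is therefore no reason to abandon the confirmatory trial, and a merely lower TPTX rate is weak support for it. An absence of higher morbidity cannot be established with 50 per arm.

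The figures rest on an assumed two-sided 5% test and on the article's literature rates, and they assume all 50 per arm are evaluable. With about 43 per arm the Fisher range is 7–23%, so the conclusion does not depend on losses. Randomisation, endpoint, sample size and planned analysis are not affected.

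**What to change.** 1. In the closing paragraph under Surgeon's expertise bias, delete the significance condition.
2. In the opening paragraph of the Discussion, remove proof of a smaller rate as the condition for launching the confirmatory study.
3. In their place, state that the pilot reports each arm's 36-month recurrence rate and the risk difference with 95% confidence intervals. The decision to proceed and the size of the next trial then rest on those intervals and on a clinically worthwhile difference or margin, not on pilot significance or the observed pilot difference.
4. In the abstract's Discussion, say that any change of practice would follow only the confirmatory trial, as the closing paragraph already does, and that 50 per arm cannot establish an absence of higher morbidity (0/50 events still allows up to 7.1%).

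A numerical go/no-go threshold is not needed for this correction. At this size a permissive interval rule also discriminates poorly. For example, with 6 points assumed as worthwhile, proceeding unless the Newcombe interval excludes that reduction would go ahead in 98% of pilots at 10% vs 4%, but also in 87% when both rates are 10%.

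The cost is wording only: no change to sample size, data collection or analysis. The downside is that the stated conclusions become more modest.

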## Abbreviations

CAEK - Chirurgische Arbeitsgemeinschaft Endokrinologie (Study Group of Endocrine Surgeons);

KKS - Koordinierungszentrum für Klinische Studien (Coordination Centre for Clinical Trials);

MRCT - multi-centre randomized controlled trial;

PTX - Parathyroidectomy;

SDGC - Studienzentrum der Deutschen Gesellschaft für Chirurgie (Study Centre of the German Surgical Society);

sHPT - secondary hyperparathyroidism;

SPTX - subtotal parathyroidectomy;

TPTX+AT - Total parathyroidectomy with autotransplantation and with routinely performed thymectomy;

TPTX - Total parathyroidectomy without autotransplantation and without routinely performed thymectomy;

PTH - Intact parathyroid hormone.
